## Abstract

**Background and aims:**

Predicting progression and prognosis in Interstitial Lung Diseases (ILD), especially Idiopathic Pulmonary Fibrosis (IPF) and Progressive Pulmonary Fibrosis (PPF), remains a challenge. Integrating patient-centered measurements is essential for earlier and safer detection of disease progression. Home monitoring through e-health technologies, such as spirometry and oximetry connected to smartphone applications, holds promise for early detection of ILD progression or acute exacerbations, enabling timely therapeutic interventions.

**Methods:**

The European ILD Registry Algorithm for Self-Assessment in ILD (eurILDreg ASA-ILD), developed by all eurILDreg principal investigators, includes questionnaires on symptom burden, respiratory infections, and quality of life (EQ5D VAS, K-BILD, LCQ). The algorithm also incorporates spirometry and oxygen saturation measurements, both at rest and during exercise (one-minute sit-to-stand test, 1STST). This ASA-ILD algorithm is integrated into the patientMpower Ltd. smartphone application, used for patient-led monitoring, research, and clinical care since 2016, and available on both Apple and Android platforms.

**Discussion:**

For patient-centered measurements, participants in the multicenter eurILDreg study will receive a patientMpower account, a handheld clinical-grade spirometer (Spirobank Smart, MIR, Italy), and a pulse oximeter (Nonin Medical, Inc. Plymouth, MN, USA), along with usage instructions. Artificial intelligence software (ArtiQ) will analyze spirometry maneuvers in real-time, ensuring compliance with recent ERS/ATS criteria and providing automated feedback. Pulse oximetry is integrated into the exercise testing within the application, following an automated in-app protocol developed with clinician involvement for safety and accuracy. The application will send reminders to participants to complete patient-reported outcome measures (PROMs) according to the study protocol.

**Conclusion:**

This study is designed to explore the potential of e-Health technologies, such as home monitoring via spirometry and oximetry, integrated with the eurILDreg ASA-ILD algorithm and patientMpower app, to improve early detection and management of ILD. A pilot trial showed promising adherence to spirometry, indicating that digital health interventions could enhance patient care and outcomes in ILD.

**Trial registration:**

The ethics committee of the Justus-Liebig-University of Giessen has approved the eurILDreg and this substudy with the protocol reference number 111/08. The research was conducted strictly according to the principles of the Declaration of Helsinki. Patients were included into the registry upon having signed the informed consent. The eurIPFreg and eurIPFbank are listed in ClinicalTrials.gov (NCT02951416). EurILDreg is registered in German Clinical Trials Register, DRKS 00028968.

## Background

Interstitial lung diseases (ILDs) are a diverse group of chronic lung diseases affecting the respiratory unit of the lung, which are historically classified in four groups: ILDs with a known cause, idiopathic interstitial pneumonias (IIPs), granulomatous disorders, as well as rare ILDs [1]. Course and prognosis of ILD varies significantly between different entities [2]. Some ILDs are reversible, other ILDs have the potential for stabilization, but fibrotic ILDs are often progressive (progressive pulmonary fibrosis, PPF) and ultimately fatal, especially idiopathic pulmonary fibrosis (IPF) [3,4]. Therefore, pharmacological and non-pharmacological treatment strategies differ between ILDs and even within the same diagnosis. Likewise, care needs may differ within ILD entities [5]. Currently, there are no routinely used biomarkers which can accurately predict disease course for individual patients [6,7].

The concept of patient-centered ILD care is well-recognized but remains challenging. While patients and healthcare providers understand the importance of focusing on patient needs, preferences, and collaboration, implementing these practices in real-world settings is difficult. This difficulty is due to limited time and resources available to healthcare professionals, which can hinder their ability to fully engage in patient-centered care practices [8].

E-Health technologies, exemplified by innovations such as home monitoring, have the capacity to foster patient-centered care and enhance healthcare quality through the utilization of information communication technology [9]. This allows remote exchange of data between patients and healthcare professionals and enables monitoring, research and management of long term conditions [10]. Frequent home monitoring, utilizing physiological measures, and Patient-Reported Outcome Measures (PROMs), has the potential to enable early detection of disease progression and may allow timely intervention, especially in IPF and PPF. Spirometers and oximeters connected to smartphone applications provide a suitable solution for physiological assessment [11].

In this regard, home monitoring has gained increasing attention in the last years [12,13]. Few studies using daily handheld spirometry have been performed in ILD patients [14]. These studies showed that home-based measurement of pulmonary function using a handheld spirometer is, in principle, feasible, reliable and has an acceptable variability [15]. Moreover, in some studies home spirometry has shown to be more sensitive in predicting disease progression and mortality than in-hospital spirometry [16,17]. However, data from randomized clinical trials have shown that self-measurements must be assessed for quality and filtered for inconsistent and implausible data. Overall, home spirometry presents an attractive home monitoring approach suitable for both clinical practice and research.

Another commonly used physiological measure in ILDs is the 6-minute walking test (6MWT), which evaluates exercise capacity and exercise-induced hypoxemia [18]. This test is frequently performed in hospitals, however, it would be challenging to perform a 6MWT at home due to the lack of standardized environment for the testing (i.e., availability of a 30-m corridor) [19]. In recent years, the 1 minute sit to stand test (1STST) has been proposed as a reliable, safe alternative to evaluate exercise capacity in patients with ILD; the 1STST is much easier to perform at home, as only a chair is needed [20].

## Methods

### Objectives

The primary objective of this project is to develop an algorithm for self-assessment (ASA) of symptom burden, respiratory infection surrogates, and quality of life (QoL: EQ5D VAS, K-BILD, LCQ), and to implement this algorithm in the patientMpower (pMp) app. Additionally, we aim to include spirometry tests and measurements of oxygen saturation at rest and during exercise (using a 1STST) into the ASA-ILD.

### Inclusion and exclusion criteria

Patients with ILD have been recruited from ILD centers in Giessen (Germany), Barcelona (Spain), and Catania (Italy) since April 2023. Recruitment at other European registry for Interstitial Lung Diseases (eurILDreg) sites is pending ethics approval and is expected to begin soon. Inclusion criteria require patients to be 18 years or older, diagnosed with ILD according to current guidelines, and confirmed through local multidisciplinary discussion (MDD) boards. Exclusion criteria include inability to comply with smartphone and app requirements, as determined by the investigator and/or patient, lack of internet access, and no intention to participate in measurements within the subsequent study year. The study also includes drop-out criteria such as low compliance, loss or misuse of medical devices, and progression to clinical conditions requiring palliative care. In cases of drop-out, data collected up until the point of withdrawal will be included in the final analysis, provided it meets predefined quality and completeness standards.

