### Study endpoints

Primary endpoint:

Serial lung function measurement (including forced vital capacity, FVC) and oxygen saturation measurements throughout the one-year study period.

Secondary endpoints:

Comparison of serial lung function measurements obtained from home and hospital spirometry, focusing on: [1] comparing the reproducibility of spirometry between home and hospital settings, and [2] evaluating the accuracy of home spirometry in identifying reliable progression trajectories of lung function over time.Assessment of participant adherence to scheduled measurements.Exploration of correlations between pulmonary function tests and PROMs at baseline, 3 months, 6 months, and 12 months.

Exploratory endpoints:

Examination of participant adherence to spirometry and 1STSTMonitoring of changes in Health-Related Quality of Life (HRQoL) and symptom burdenAnalysis of hospitalizations rates, disease progression, acute exacerbations, together with overall outcomesEvaluation of healthcare provider and participant satisfaction, along with their experiences with the pMp applicationAssessment of adherence to the home monitoring by evaluating data set completeness, including both pulmonary function and PROMs.

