To mitigate device fatigue, the app will limit the frequency of required inputs, reducing participant burden while still capturing essential data. This strategy aims to maintain engagement and prevent participants from feeling overwhelmed by frequent interactions. Non-compliant patients, defined as those who have not taken any measurements for four consecutive weeks, will be categorized into a separate study subgroup. Sensitivity analyses will assess the impact of non-compliance on primary and secondary outcomes, allowing differentiation between compliant and non-compliant participants. This will also facilitate the exploration of potential reasons for non-compliance, such as age, disease severity, or technical difficulties.

By integrating regular follow-up mechanisms, tailored support for diverse patient needs, and a clear plan for managing non-compliance, this strategy aims to enhance overall adherence, minimize data loss, and ensure the reliability of the study’s findings.

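### Drop-outs' data must pass a completeness standard although adherence, completeness and progression are endpoints, and the low-compliance drop-out rule is not reconciled with the retained non-compliant subgroup

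*Protocol article*

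**What the plan says.** In the protocol article, the section Inclusion and exclusion criteria says: "The study also includes drop-out criteria such as low compliance, loss or misuse of medical devices, and progression to clinical conditions requiring palliative care". Of patients who drop out it says that "data collected up until the point of withdrawal will be included in the final analysis, provided it meets predefined quality and completeness standards". The standards are called predefined, but the article does not give them.

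The section Study endpoints names these outcomes:
- Primary: serial lung function, including FVC, and "oxygen saturation measurements throughout the one-year study period".
- Secondary: "evaluating the accuracy of home spirometry in identifying reliable progression trajectories of lung function over time", and "Assessment of participant adherence to scheduled measurements".
- Exploratory: hospitalisation, progression, exacerbation and overall outcome, and adherence judged by how complete each data set is.

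The section Strategies to ensure patients' compliance takes a different line on non-compliance: "Non-compliant patients, defined as those who have not taken any measurements for four consecutive weeks, will be categorized into a separate study subgroup". It adds that "Sensitivity analyses will assess the impact of non-compliance on primary and secondary outcomes", and names disease severity as one possible reason for non-compliance.

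**The concern.** Two of the drop-out criteria, low compliance and palliative progression, are close relatives of things the study sets out to measure. Leaving home measurement for either reason is therefore informative about the endpoints. The completeness condition adds a second selection step. Among drop-outs, it admits those who measured a lot and may turn away those who measured little. For an endpoint defined by completeness this is circular. For the FVC and saturation course it matters if sparse data go with more severe disease, a link the article itself treats as possible.

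Two results are at stake. Reported adherence could be too high, because the least adherent patients may not be counted. Reported decline could be too shallow, because patients who progressed and stopped early may not be counted either. The second bears on the study's stated interest in early detection of progression.

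There is also an unresolved conflict. One section ends participation for low compliance; another keeps non-compliant patients as an analysed subgroup. If the first governs and the completeness standard is applied, the promised sensitivity analyses may lose the sparse data they need.

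**Working it through.** The article states no sample size, slope or threshold on this point, so there is no planned figure to reproduce. The check sets the sections side by side and then uses the pilot figures to gauge reach.

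**1. Overlap of drop-out criteria and endpoints**

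| Rule for drop-outs | Matching endpoint |
|---|---|
| Low compliance ends participation | Adherence (secondary) |
| Palliative progression ends participation | Progression trajectories (secondary); disease progression and overall outcome (exploratory) |
| Data must meet a completeness standard | Adherence judged by data set completeness (exploratory) |

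The completeness condition is worded for drop-outs. The article does not say whether patients who stay face the same test.

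**2. Pilot counts** (section Results of a pilot trial: 25 patients, 12 weeks)
- Spirometry: 25 × 0.84 = 21 adherent, 25 × 0.16 = 4 not.
- 1STST: 25 × 0.64 = 16 adherent, 25 × 0.36 = 9 not.

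**3. How complete a non-adherer's data can be.** Non-adherent patients were at 0% by week 8, so each has data in at most 7 weeks.
- Against a one-year schedule: 7/52 = 13%.
- Against the time until a four-week gap (weeks 8 to 11) is complete: 7/11 = 64%.
- If adherence falls linearly from 100% in week 1 to 0% in week 8, the total is 4 week-equivalents: 4/52 = 8% and 4/11 = 36%.

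A threshold above about 13% of the year would exclude every such patient. A modest threshold applied only to the time before withdrawal might exclude none. The effect depends on a definition that is not shown.

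**4. Reach in the main study** (62 recruited, pilot rates assumed): 62 × 0.16 = 9.9 and 62 × 0.36 = 22.3, so about 10 to 22 patients. The upper figure is non-adherence to the 1STST. Such a patient may still do spirometry and so fall outside the four-week definition.

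**5. Effect on adherence, extreme case.** If every non-adherer were excluded, the adherent share would go from 84% (spirometry) and 64% (1STST) to 100% by construction.

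The shift in mean adherence is less certain. Suppose the pilot's 91% mean for spirometry covers all 25 patients on a weekly scale. Then adherers average (0.91 − 0.16m)/0.84, where m is the non-adherers' mean. The linear fall (m = 4/12 = 0.33) gives 1.02, which is impossible. The maximum (m = 7/12 = 0.58) gives 0.97. On that reading, excluding all non-adherers would lift 91% to between 97% and 100%. The article does not say which patients or which scale the 91% refers to.

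**6. Effect on mean FVC slope, illustration only.** No slope or share of progressors is in the documents. Let q be the share of progressors, f the fraction of them lost from analysis, and s₁ and s₂ the slopes of progressors and others.
- True mean = q·s₁ + (1 − q)·s₂.
- Observed mean = [q(1 − f)·s₁ + (1 − q)·s₂]/(1 − qf).

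Assume s₁ = −300 and s₂ = −50 mL/yr:

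| q | f | True | Observed | Understated by |
|---|---|---|---|---|
| 0.10 | 0.25 | −75 | −69 | 8% |
| 0.20 | 0.50 | −100 | −78 | 22% |
| 0.30 | 1.00 | −125 | −50 | 60% |

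Other assumed slopes, with all progressors lost, give 17% (q = 0.10, −300 and −100: −120 versus −100) to 44% (q = 0.20, −400 and −80: −144 versus −80).

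**The case against.** The strongest reply is that nobody is removed. Drop-outs' data up to withdrawal are kept if they meet the standard, and the standard could be as light as one acceptable session. It is called predefined, and an article may leave its content to the full protocol or analysis plan. Non-compliant patients are kept as a subgroup with sensitivity analyses. The study is non-comparative, states no mean-slope estimate or hypothesis, and lists completeness and clinical events as exploratory. Filtering self-measured data for quality is justified in the Background.

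Most of this stands, and it rules out several stronger readings that a reader might infer:
- *Progressors and non-adherers are excluded altogether.* The text keeps their qualifying data.
- *Adherence is estimated only after low adherers are taken out.* No sentence says so, and the compliance section points the other way.
- *Events are cut off just before they occur.* Progression comes before a drop-out for palliative progression, and nothing says that eurILDreg follow-up ends when a patient leaves this substudy.
- *The missing thresholds are themselves a fault.* They may be in a document that is not shown.

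The reply does not answer three things. A completeness condition is circular for an endpoint made of completeness; the threshold changes the size of the problem, not its nature. The low-compliance drop-out and the retained subgroup are not connected: they may be different thresholds or successive steps, but the article does not say. The compliance section offers nothing comparable for palliative drop-outs.

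**Conclusion.** The point holds in limited form. The article admits drop-outs' data subject to completeness while adherence, completeness and progression are endpoints, so any binding threshold selects on the outcome. The likely direction is overstated adherence and understated decline. For decline, this rests on sparse data going with worse disease, which the article raises as a possibility and does not establish.

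The size is unknown. The 13% bound and the 10 to 22 patients assume that the main study behaves like a 25-patient, 12-week pilot. The move to 100% adherent is an extreme that the article does not describe. The FVC percentages rest wholly on assumed slopes, shares and losses. What can be said firmly is that the two sections need reconciling and that the completeness condition should not stand as worded.

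**What to change.** 1. Reconcile the two sections: state whether low compliance ends participation or defines a retained subgroup, and how it relates to the four-week definition.
2. Delete the words 'and completeness' from the condition on drop-outs' data, so that every measurement passing the per-manoeuvre quality check is analysed, however few a patient has.
3. Keep all enrolled patients in the adherence denominators, counting scheduled measurements after a low-compliance drop-out as not done.
4. Report palliative progression and death as outcomes, using registry follow-up after drop-out where eurILDreg collects it (to be confirmed). Add a sensitivity analysis for informative drop-out; using all available data in a longitudinal model does not by itself deal with drop-out that depends on unseen decline.

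The cost is protocol and analysis wording, plus an extract of registry data if follow-up continues. Reported adherence will be lower and reported decline possibly steeper. Recruitment is under way, so early action is better: outcomes not collected after drop-out may not be recoverable. The clinical rule for stopping home measurement is left as it is.

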### Ethics approval and consent to participate

The ASA-ILD algorithm is a substudy of the eurILDreg, which has been reviewed and approved by the local ethics committee (AZ 111/08, Amendment dated March 20, 2013) [21,22]. All participating sites of eurILDreg must obtain approval from their respective Medical Ethics Committees. The study will be conducted in accordance with the Declaration of Helsinki. Written informed consent will be obtained from the participants. The EurILDreg is registered in the German Clinical Trials Register under DRKS 00028968 [23].

### Study endpoints

Primary endpoint:

Serial lung function measurement (including forced vital capacity, FVC) and oxygen saturation measurements throughout the one-year study period.

Secondary endpoints:

Comparison of serial lung function measurements obtained from home and hospital spirometry, focusing on: [1] comparing the reproducibility of spirometry between home and hospital settings, and [2] evaluating the accuracy of home spirometry in identifying reliable progression trajectories of lung function over time.Assessment of participant adherence to scheduled measurements.Exploration of correlations between pulmonary function tests and PROMs at baseline, 3 months, 6 months, and 12 months.

Exploratory endpoints:

Examination of participant adherence to spirometry and 1STSTMonitoring of changes in Health-Related Quality of Life (HRQoL) and symptom burdenAnalysis of hospitalizations rates, disease progression, acute exacerbations, together with overall outcomesEvaluation of healthcare provider and participant satisfaction, along with their experiences with the pMp applicationAssessment of adherence to the home monitoring by evaluating data set completeness, including both pulmonary function and PROMs.

### Study design

PMp applications have been specifically developed for ILD and have been used in patient-led monitoring, research, and clinical care pathways since 2016. The app is available for both Apple and Android operating systems.

The eurILDreg ASA-ILD works with clinical-grade medical devices, including a spirometer (Spirobank Smart, MIR, Italy), and a pulse oximeter (Nonin Medical, Inc., Plymouth, MN, USA), both of which can be seamlessly connected to the mobile pMp application via Bluetooth. At the time of inclusion, participants will be provided with a pMp account, a handheld spirometer, and a pulse oximeter, along with detailed instructions. Via the pMp application, online home spirometry, measurements of oxygen saturation at rest and during a 1STST, completion of PROMs, and a daily symptom check are conducted. The app shows data from the nearest weather station indicating outdoor pollution level.

Patients will receive comprehensive guidance on study procedures, including instructions for conducting lung function and exercise tests (Fig 1). They will then download the application in their native language, input login credentials, and establish Bluetooth connections with devices to ensure accurate measurements. Study participants will be asked to conduct daily lung function assessments and monitor oxygen levels both at rest and during exercise each morning, around the same time to reduce variability. Before these assessments, patients share their daily state by responding to a brief set of questions (Symptoms-Check). Engaging with the measurements requires approximately 3–5 minutes of the patient’s time each day.

**Fig 1 pone.0316484.g001:**
[figure not shown]
ASA-ILD measurement algorithm. Abbreviations: ASA-ILD, algorithm for self-assessment in interstitial lung diseases.

Spirometry maneuvers performed using the application are analyzed in real time with artificial intelligence software (ArtiQ) for compliance with recent ERS/ATS criteria [24,25]. Pulse oximetry is used for exercise testing within the app, following an automated protocol developed with clinician involvement, ensuring safety and accuracy. The app also sends reminders to participants to complete PROMs at the frequency specified in the study protocol.

The finalized ASA-ILD protocol ensures that eurILDreg patients who meet study eligibility criteria will receive study information through their ILD treatment centers. Patient instructions for using the spirometer include inserting batteries, ensuring it remains in perpetual pairing-ready mode, changing batteries every 4–6 months, cleaning the mouthpiece and rotor weekly, and demonstrating proper device handling. Participants using the Nonin Pulse Oximeter are advised to replace batteries every 6 months or as needed for optimal performance, and to maintain a clean, dry finger for accurate readings. Additionally, participants are requested to complete the EQ5, KBILD, and LCQ questionnaires every three months, providing valuable ongoing research data.

Following a demonstration conducted by trained personnel at the ILD center, patients proceed by tapping the red ‘plus’ sign on the home screen of their smartphones, selecting ‘add spirometry’ and allowing a moment for the app to establish a connection to the spirometer. Once connected, they select ‘understood’ to initiate the test and to do the spirometry measurement (blow through visual and audible cues). They then receive feedback on the test, including any substandard techniques, and are asked to repeat the measurement. Any improper exhalation detected prompts an explanatory error message and asks to repeat the measurement. The spirometry measurements adhere to the recent ERS/ATS guidelines in regard to technical standards on interpretive strategies for lung function tests [24,25].

For the 1STST, patients need a chair with a standard height of around 46 centimeters, without armrests, positioned against a wall. Patients are instructed to sit upright with their knees and hips bent at 90-degree angles, feet placed flat on the floor hip-width apart, and arms resting firmly on their hips. Prior to the test, the patient undergoes a pre-test check of their oxygen saturation to ensure it is above 94%. Additionally, the test will alert the patient and stop if they begin desaturating during the test. During the 1-minute test, patients perform repetitions of standing up and sitting down in this specific position at a pace comfortable for them, without using their arms for support. They aim to complete as many repetitions as possible within the allotted time. If needed, patients are allowed to take short rests during the 1-minute period. In the application, patients document the number of repetitions they achieve, as well as report their level of breathlessness (Borg Dyspnea score). Oxygen saturation levels are recorded automatically. This process ensures accurate and comprehensive data collection for the study.

Patients assess their data by selecting the “my data” option at the bottom of the home screen and choosing a timeframe from the options at the top of the screen. Patients are encouraged to contact the clinic for any assistance needed with device use. Automated alerts are not generated for healthcare providers in the event of alterations in pulmonary function, oxygen saturation or PROMs. In general, during the study period, patients are not called up or re-contacted outside their visits to the center.

Prior to initiating the exertion test, patients will undergo a pre-test oxygen saturation assessment. If their oxygen saturation is below 94%, the test will not proceed to mitigate the risk of desaturation. Similarly, if a patient’s oxygen saturation drops below 94% during the test, it will be immediately discontinued to prevent further desaturation.

Although, the study team will not actively monitor the real-time data collected through the application; however, patients will have access to their data and will receive clear guidance on how to interpret it. While the app itself will not prompt any actions based on the readings, patients will be instructed on the appropriate steps to take should they observe concerning trends. For example, if patients notice a significant decline in their lung function readings, they will be advised to contact their physician promptly. This approach empowers patients to take an active role in managing their health while ensuring they know when to seek professional assistance.

The study protocol includes strategies for addressing data transfer issues. Patients will see an error screen with a description of the connection issue they are experiencing, in case of failed or incomplete data transfer. Additionally, a support line will be available to guide patients in resolving these issues.

While the real-time data will not directly influence the primary and secondary outcomes during the study, it provides valuable insights into patient trends and health status. These data will be analyzed post-study to identify patterns and correlations that may contribute to understanding the effectiveness of the remote monitoring approach. Additionally, the study design will include a framework for assessing how variations in real-time data correlate with changes in primary and secondary outcomes, enabling us to explore the potential impact of real-time monitoring on patient care and health outcomes in the future. This comprehensive analysis will help determine whether integrating real-time data into clinical decision-making enhances patient management and improves health outcomes in patients with ILD.

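### The planned analysis cannot help show that acting on real-time data improves outcomes: the study does not build the data into care, has no comparator, and correlates app data with outcomes partly made of the same data

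*Protocol article*

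**What the plan says.** All of this is in the protocol article, under Methods.

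- **The inference.** The end of Study design says: "This comprehensive analysis will help determine whether integrating real-time data into clinical decision-making enhances patient management and improves health outcomes in patients with ILD".
- **The analysis meant to support it.** The sentence before promises "a framework for assessing how variations in real-time data correlate with changes in primary and secondary outcomes".
- **How the data are used during the study.** Study design says that "the study team will not actively monitor the real-time data collected through the application". It adds: "Automated alerts are not generated for healthcare providers in the event of alterations in pulmonary function, oxygen saturation or PROMs". It also says: "In general, during the study period, patients are not called up or re-contacted outside their visits to the center". The app itself triggers nothing. Participants can see their own readings and are told to get in touch with their doctor if lung function falls markedly.
- **The role given to the data.** The same part of Study design says that "the real-time data will not directly influence the primary and secondary outcomes during the study".
- **The outcomes.** Under Study endpoints the primary endpoint is "Serial lung function measurement (including forced vital capacity, FVC) and oxygen saturation measurements throughout the one-year study period". The secondary endpoints are home against hospital spirometry, adherence, and correlations of lung function with PROMs. Hospitalisations and acute exacerbations are exploratory.

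**The concern.** Whether building data into clinical decisions improves outcomes is a causal question. Answering it needs some patients whose care used the data and some whose care did not. The article describes neither a planned use of the data in care nor a comparison group.

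The analysis offered instead is a correlation, and its two sides share measurements. The app records home spirometry, oxygen saturation, PROMs and symptoms, and most of the primary and secondary outcomes draw on those records. A positive correlation could arise from the shared readings alone, and a reader guided by the closing sentence could take it as evidence that monitoring improves care.

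**Working it through.** The article gives no sample size calculation, alpha or power, so there is no planned figure to reproduce. The check has three steps.

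**Step 1: is there an integration contrast?**

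| Route from data to care | What the article says | Where |
|---|---|---|
| Study team | no active monitoring | Study design |
| Clinicians | no automated alerts | Study design |
| App | prompts no action | Study design |
| Contact between visits | in general none | Study design |
| Data flow | monthly to the app database, periodically to the registry | Data transfer and protection |
| Patient calls the doctor | possible; same advice to all | Study design |
| Control arm, site contrast or historical group | none described | whole article |

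No participant is assigned to care that uses the data, and the one informal route applies to everyone alike. The exposure has no planned variation, so its effect is not identified at any sample size.

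**Step 2: where do the outcomes come from?**

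| Outcome | Source | Overlap with app data |
|---|---|---|
| Serial FVC and oxygen saturation (primary) | recorded by the app; the article does not expressly limit it to home readings | large |
| Adherence | count of scheduled measurements made | large |
| Home against hospital spirometry | home half from the app, hospital half not | partial |
| Lung function against PROMs | PROMs completed in the app | partial |
| Hospitalisation, acute exacerbation (exploratory) | outside the app | none evident, but not in the framework, which names primary and secondary outcomes |

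**Step 3: can overlap alone create association?** The documents give no SDs, windows or summary measures, so both illustrations rest on assumptions.

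*(a) Same series, overlapping windows.* Assume equally spaced readings that are pure white noise with variance v, and no true differences in decline. Let S be the sum of squared centred times over the year and S1 the same over the first fraction f.

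- var(b1) = v/S1, var(b) = v/S, cov(b1, b) = v/S
- corr(b1, b) = sqrt(S1/S), which is about f^1.5 because S grows as the cube of the number of readings
- f = 0.5: 0.5^1.5 = 0.354

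If a sample of 62 (the number recruited so far, not a stated target) showed exactly this r, then t = 0.354 × sqrt(60/(1 − 0.125)) = 2.93, two-sided p about 0.005. With the second-half slope as outcome no readings are shared, the covariance is 0 and so is the expected correlation.

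*(b) App change against the home-minus-hospital difference.* Let H = T + e_h (home change) and C = T + e_c (hospital change), with independent errors and no effect of integration. With s = SD(T)/SD(e_h) and q = SD(e_c)/SD(e_h):

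corr(H, H − C) = 1/sqrt((s² + 1)(1 + q²))

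| s | q = 0.5 | q = 1 | q = 2 |
|---|---|---|---|
| 0 | 0.89 | 0.71 | 0.45 |
| 1 | 0.63 | 0.50 | 0.32 |
| 2 | 0.40 | 0.32 | 0.20 |

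Even against hospital FVC alone, corr(H, C) = s²/sqrt((s² + 1)(s² + q²)), which at s = 1 is 0.63, 0.50 and 0.32 for the same three values of q. That would show agreement between two measurements, not benefit from acting on one of them.

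**The case against.** The best case for the article has five parts.

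1. **The wording is hedged.** The analysis is only to help determine the answer, the sentence before speaks of exploring potential impact in the future, and the Conclusion of the abstract describes an exploratory study. A reader might infer that the plan claims a definitive answer; the text does not go that far. The hedge still does not rescue it, because data with no contrast cannot help determine this effect.
2. **The correlation is not spurious by necessity.** A reader might infer that a positive result is guaranteed. It is not. The article fixes no window or summary, and the 0.35 above rests on an overlapping-window specification that no passage plans. Variations may mean variability, and under white noise the first-half SD has no expected correlation with the later slope. Hospital spirometry is an independent source, so overlap with the first secondary endpoint is only partial. This stands in full.
3. **No flat contradiction about influence.** A reader might see one between "the real-time data will not directly influence the primary and secondary outcomes during the study" and patients acting on their readings. The adverb *directly* leaves room for that indirect route, which the same passage openly describes. The wording is imprecise, not contradictory.
4. **Part of the answerable question is already there.** A secondary endpoint covers how accurately home spirometry tracks progression, and clinical events are listed as exploratory. This stands, but the framework behind the disputed sentence does not name those events.
5. **Details belong in the full protocol or SAP.** True of windows and summaries. It does not apply to the inference: the article itself states both the claim and the absence of integration, and no analysis plan can supply a missing exposure contrast.

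The one contrast in the article, compliant against non-compliant patients, concerns taking measurements. The article itself names age and disease severity among the possible reasons for non-compliance, so it cannot stand in for integration.

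**Conclusion.** The sentence is wrong as written; severity is moderate. The effect of integrating real-time data into care is not estimable from this cohort at any sample size. That conclusion rests only on what the article states about monitoring, alerts, app actions and the uniform provision of devices.

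The overlap between app data and outcomes is a weaker, conditional point. It is large for the serial measurements and adherence and partial for the other two secondary endpoints. It can generate association without benefit: r about 0.35 under the white-noise, overlapping-window assumption, and 0.20 to 0.89 for the home-minus-hospital difference over the assumed SD ratios. It need not do so under other choices.

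A reader might infer that the study as a whole is compromised. The documents do not support that: the primary objective is to develop and implement the algorithm, and no listed endpoint tests an integration effect.

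**What to change.** 1. Delete the sentence on integration into clinical decision-making, or limit it to a descriptive, hypothesis-generating aim. A claim about integration would need a comparative study.
2. Define the framework as a prediction analysis: home FVC or oxygen saturation trend or variability in an earlier window against later outcomes measured outside the app and already listed (hospital spirometry decline, hospitalisation, acute exacerbation). Predictor and outcome windows should not overlap.
3. Beside the statement on direct influence, say that patients see their readings and may contact their physician, so indirect feedback on outcomes is possible.

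The cost is a more modest stated claim and a little more analysis work. These changes use outcomes under Study endpoints. Adding physician contacts, treatment changes or death would go further: the article does not show that these are collected, so they should not be assumed to come free.
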